#### *Analysis of individual questions from TEC survey*

We will analyze 12 dichotomous (yes/no) patient experience questions from the trained exit client (TEC) survey. Initially, binomial models with a log link (relative risk) or identity link (risk difference) will be used to analyze these data. However, it is well-known that models assuming a binomial distribution often fail to converge (Spiegelman, 2005), and if we find widespread convergence failure for either of the link functions then we will employ models that assume a Poisson distribution. If convergence issues still persist then we will also explore alternative modelling for random effects (e.g., GEE). Significant differences ( $P < 0.05$ ) with greater proportions of positive experiences in the PCC intervention group will support the hypothesis that the PCC intervention was more effective compared to the control. Results will be presented in terms of risk ratios (95% CI) and risk differences (95% CI). Forest plots with these estimates and 95% CIs will also be used to visually display the results. Additionally, we will present the absolute percentages to assess where the improvements any improvements are occurring (e.g., 40% to 50% vs 85% to 90%).

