## **Subgroup analyses**

The primary subgroup analyses of interest will be to assess whether there is evidence of heterogeneity in treatment effects among clusters by stratifying the analyses by healthcare facility (“horizontal” analysis) and heterogeneity in treatment effects across time by stratifying analyses across periods (“vertical” analysis) (analysis terminology as per White et al., 2018).

In addition to the stratified analyses of primary interest (across clusters and periods), we will also assess the difference between the intervention and control groups for the following subgroups:

- Care Status (in care, LTFU)
- Intervention and control group (TEC vs Exit comparison only)
- Sex
- Age (<25, 25-44, >45)
- Clinic Size and Type
- Improvement index by facility
- PCC dose - when finalized
- Advanced HIV Disease at enrollment in care (WHO Stage 3 or 4, CD4<200)

For those subgroups that appear to have a difference with regard to the intervention effect, we will formally test for an interaction between the intervention and the subgroup.

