## Sample size estimation

Assuming that 65% of individuals reported a positive patient experience at baseline and a very conservative intraclass correlation between facilities of 0.2, we estimated that we would be able to detect a 15.0% difference between intervention and control arms with 80% power and at  $p < 0.05$ .

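### SAP 4.0 tests TEC subgroup interactions only where a difference already appears, with no stated criterion, so p-values from the tests that are run cannot be read at face value

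*Combined protocol and SAP*

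**What the plan says.** SAP section 4.0, under Subgroup analyses, first names stratification by facility and by period as the analyses of main interest. It then adds a second set: "we will also assess the difference between the intervention and control groups for the following subgroups". Eight items follow: care status, a TEC-versus-exit-survey comparison, sex, age in three bands, clinic size and type, a facility improvement index, PCC dose (still to be finalised), and advanced HIV disease at enrolment.

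The rule for formal testing is one sentence: "For those subgroups that appear to have a difference with regard to the intervention effect, we will formally test for an interaction". The section gives no criterion for an apparent difference, no significance level for the interaction tests and no multiplicity rule. It does not say which outcome or which intervention contrast triggers a test.

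No other section plans interaction tests for all TEC subgroups. The only other interaction mentioned is the slope term under Quantile regression.

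**The concern.** The observed gap between strata decides whether that same gap is tested. A p-value is uniform under the null only if the test would have been run whatever the data showed. Once small gaps are filtered out, the p-values that remain are shifted towards small values, and a reader who takes p<0.05 as a 5% event is misled.

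The trigger is also loose. The SAP analyses 12 survey questions, a sum score and principal-component scores, each with an early (up to 6 months) and a late (over 6 months) intervention contrast. A subgroup can look different on one of these and not on another.

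What is at stake is how far to trust any claim that the intervention changed client experience more in one group than in another. The primary outcome, treatment failure, is not affected.

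**Working it through.** **Inputs.** The testing rule is from SAP 4.0, Subgroup analyses. The level of 0.05 is the one stated for the individual TEC questions ("Significant differences ( $P < 0.05$ ) with greater proportions of positive experiences in the PCC intervention group"); it is assumed to carry over, two-sided. The threshold for an apparent difference is not in the documents and is varied below. The SAP gives no error rate or power for interactions, so there is no planned figure to reproduce. Its TEC sample-size statement ("we estimated that we would be able to detect a 15.0% difference between intervention and control arms with 80% power") concerns the overall contrast, and nothing here depends on it.

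**Step 1: two-level subgroup, null interaction.** Let Z be the between-stratum difference divided by its standard error, so Z ~ N(0,1). If the test is run only when |Z| > c, with c ≤ 1.96, then

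P(p<0.05 | tested) = 0.05 / P(|Z| > c)

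| c (SE) | P(tested) | P(p<0.05 given tested) |
|---|---|---|
| 0 | 1.000 | 5.0% |
| 0.5 | 0.617 | 8.1% |
| 1.0 | 0.317 | 15.8% |
| 1.25 | 0.211 | 23.7% |
| 1.5 | 0.134 | 37.4% |

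P(tested and p<0.05) is 5% in every row. The screen changes the rate among tests that are run, not the rate per interaction.

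**Step 2: age.** The formula does not apply to three levels. Simulation with three equal-SE strata, a screen on the largest pairwise difference and a 2-df test gives 8.7% at 1.0 SE and 17.2% at 1.5 SE.

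**Step 3: other readings of an apparent difference.** These were simulated with stratum standard errors derived from the sex rows of Table S4 and a common effect of 0, -5.4 or -16.9 points (the last two are the overall Table S4 effects).

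| Screen | P(p<0.05 given tested) |
|---|---|
| One stratum significant, the other not | 15–33% |
| An estimate outside the other stratum's 95% CI | 22–28% |
| Gap above 5 points | 9–10% |
| Gap above 10 points | 24–27% |
| One estimate at least twice the other in size | 4–31% |
| Opposite signs | 10–14% (74% at a common effect of -16.9, but then tested in only 0.2% of cases) |
| Non-overlapping CIs | 100% |

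**Step 4: multiplicity, a separate matter.** Five listed factors are baseline-defined: care status, sex, age, clinic size and type, and advanced HIV disease. Unadjusted, the chance of at least one false interaction is 1 - 0.95^5 = 22.6% if independent, and about 18% at an assumed correlation of 0.5, per outcome and contrast. Counting all seven possible modifiers gives 1 - 0.95^7 = 30.2%. A screen of up to 1.96 SE on the interaction itself leaves these figures unchanged; other screens can only lower them.

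**Step 5: what the rule would meet in this trial.** Table S4 gives stratified risk differences for a bad client experience. With SE = CI width / 3.92 and strata treated as independent (an approximation, since they share facilities):

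- Sex, late: -24.0 - (-9.2) = -14.8; SE = √(5.51² + 5.23²) = 7.60; z = -1.95; p = 0.051.
- Care status, late: -9.2; SE 7.54; z = -1.22; p = 0.22.
- Sex, early: -1.3; SE 7.97; z = -0.16; p = 0.87.
- Care status, early: -5.8; SE 7.95; z = -0.73; p = 0.47.
- Age, early (28.5, -6.0, -15.2; SEs 15.8, 5.3, 7.5): Q = 6.26 on 2 df; p = 0.044.
- Age, late: not computable, because two CIs were not estimable.

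On the late contrast, a 1.0 SE screen would send both sex and care status to a test, a 1.5 SE screen only sex. On the early contrast neither would be tested. What gets tested turns on choices the SAP leaves open.

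**The case against.** The strongest reply is that a screen can only remove tests. The chance that a given null interaction is both tested and significant stays at or below 5%, and for a screen on the same statistic every significant result would also have been significant had all been tested. A reader might infer that the rule gives these analyses a 16% to 37% type I error. The documents do not support that: they state no threshold, and the figures are conditional on testing. This part of the reply stands.

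A reader might also attribute the 18% to 23% family-wise rate to the screening rule. It is the ordinary rate for five unadjusted tests and would be the same if all were run.

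Nor do the documents show selected interaction p-values in print. Table S4 contains none. The subgroup list is set out in advance, stratified differences are planned for every item, and Table S4 shows care status, sex and age, mostly with CIs. A reader can therefore partly reconstruct the family, though Table S4 has no rows for clinic size and type or advanced HIV disease.

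Finally, this is a secondary outcome, and asking for a formal test rather than comparing strata by eye is itself a safeguard.

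None of this removes the defect. The criterion is missing, the data choose the test, and the p-values that come out are not uniform under the null.

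**Conclusion.** The point holds in a limited form. SAP 4.0 lets the observed TEC data select which subgroup interactions are formally tested, with no stated criterion, so p-values from the tests that are run should not be taken at face value.

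The size cannot be fixed from the documents. Under an assumed 1.0 to 1.5 SE screen and a two-sided 5% level, a tested null interaction would be significant about 16% to 37% of the time in a two-level subgroup and about 9% to 17% for age. Other readings run from about 4% to 100%. These are conditional rates, not an inflated error per interaction.

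The absence of any multiplicity statement is a distinct gap, worth about 18% to 23% for five unadjusted tests per outcome and contrast. The consequence is confined to effect-modification claims on client experience.

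**What to change.** Replace the conditional sentence in SAP 4.0, Subgroup analyses, with:

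> For every baseline-defined subgroup listed (care status, sex, age, clinic size and type, advanced HIV disease), an intervention-by-subgroup interaction will be fitted and its estimate and p-value reported whatever the observed difference; these analyses are exploratory, and the number of interactions tested will be stated.

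This removes the selection and makes the family visible. Holm adjustment across the subgroups is optional. It would not by itself cover the 12 questions, the scores and the two contrasts, so the exploratory label and the stated count are needed in any case.

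The cost is one sentence, a few extra model fits on data already collected, and subgroup claims that read as less definitive.

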## **Quantile regression**

In addition to variability in the central tendency as measured by the mean, there is also likely to be strong variability at the extremes of the data that may better captured via a quantile-regression analytic approach. This approach permits fitting regression lines through various quantiles of the data (e.g., 90th percentile, 10th percentile) to test how individuals at distributional extremes respond to the intervention. We will stratify these analyses by facility and examine how the response of different outcomes vary over time and in response to the intervention. To these ends, models will fit a regression line over the course of the study with an indicator variable for the intervention. We will also test whether the slope varies by the intervention by fitting a treatment x intervention interaction.

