**Figure S5. Effect of PCC Intervention on Client Experience.** Distribution of client experience scores (Panel A) represented as the sum of responses to the 12 questions on the client experience survey (range 0 to 12) during control, the first 6 months, and more than 6 months in violin plots that depict the density of client experience scores across range of response values. The red line depicts a scores of  $\leq 8$ , under which we considered the encounter a "bad experience." Solid and dashed black lines represent the median and interquartile ranges, respectively. Quantile regression (Panel B) show effect of the PCC intervention at different quantiles of client experience (e.g., from 5th to 95th quantile). The greatest effects (i.e., change to mean sum score) were seen amongst clients who reported the worst experiences (i.e., those at the lowest quantiles) with minimal to no effects seen amongst those above the 60th percentile of client experience scores (i.e., highest client experience).

| Table S4. Number Needed to Treat for PCC Intervention to Avert a Bad Client Experience (i.e., TEC sum score ≤8) in Cohort 1 |                                        |      |                                        |      |
|------------------------------------------------------------------------------------------------------------------------------------|----------------------------------------|------|----------------------------------------|------|
|                                                                                                                                    | Intervention <6m vs. Control |      | Intervention >6m vs. Control |      |
|                                                                                                                                    | Adjusted Risk Difference
(95% CI)   | NNT* | Adjusted Risk Difference
(95% CI)   | NNT* |
| Overall                                                                                                                     | -5.4
(-13.4 – 2.6)                  | 18   | -16.9
(-24.8 – -8.9)                | 6    |
| Baseline Care Status                                                                                                        |                                        |      |                                        |      |

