| 0.2                   | 8.6
(8.1-9.0)       | 9.2
(8.7-9.7)                   | 9.9
(9.2-10.7)                  | 0.7
(-0.1-1.4)                      | 1.4
(0.3-2.5)                       |
| 0.25                  | 9.1
(8.7-9.5)       | 9.6
(9.1-10.0)                  | 10.4
(9.7-11.0)                 | 0.5
(-0.2-1.1)                      | 1.3
(0.3-2.3)                       |
| 0.3                   | 9.3
(8.9-9.7)       | 10.0
(9.6-10.4)                 | 10.7
(10.0-11.3)                | 0.7
(0.1-1.3)                       | 1.3
(0.4-2.2)                       |
| 0.35                  | 9.8
(9.4-10.2)      | 10.3
(10.0-10.6)                | 10.7
(10.2-11.2)                | 0.5
(-0.1-1.0)                      | 0.9
(0.0-1.7)                       |
| 0.4                   | 10.1
(9.7-10.5)     | 10.5
(10.2-10.8)                | 10.8
(10.3-11.4)                | 0.4
(-0.1-0.9)                      | 0.7
(0.0-1.5)                       |
| 0.45                  | 10.4
(10.0-10.7)    | 10.7
(10.4-10.9)                | 11.0
(10.5-11.5)                | 0.3
(-0.1-0.8)                      | 0.6
(-0.1-1.4)                      |
| 0.5                   | 10.6
(10.3-10.9)    | 10.8
(10.6-11.1)                | 11.2
(10.7-11.7)                | 0.2
(-0.2-0.7)                      | 0.6
(-0.1-1.3)                      |
| 0.55                  | 10.8
(10.6-11.1)    | 11.0
(10.7-11.3)                | 11.3
(10.8-11.9)                | 0.1
(-0.3-0.5)                      | 0.5
(-0.2-1.2)                      |
| 0.6                   | 11.2
(11.0-11.5)    | 11.2
(11.1-11.5)                | 11.2
(10.7-11.8)                | 0.0
(-0.3-0.3)                      | 0.0
(-0.8-0.8)                      |
| 0.65                  | 11.4
(11.1-11.6)    | 11.4
(11.1-11.7)                | 11.4
(10.8-12.0)                | 0.0
(-0.3-0.3)                      | 0.0
(-0.8-0.8)                      |
| 0.7                   | 11.5
(11.2-11.8)    | 11.5
(11.2-11.8)                | 11.5
(10.8-12.0)                | 0.0
(-0.4-0.4)                      | 0.0
(-0.9-0.9)                      |
| 0.75                  | 11.9
(11.5-12.0)    | 11.9
(11.5-12.0)                | 11.9
(11.3-12.0)                | 0.0
(-0.5-0.5)                      | 0.0
(-0.8-0.8)                      |

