#### *Analysis of PCA composite axes and survey sum scores*

The analysis for these outcomes will involve two steps. In step 1, we will estimate the tetrachoric correlations between the 12 variables from the TEC survey which will subsequently be analyzed using a principal components analysis (PCA). We will use standard methods to objectively determine the # of axes to retain and interpret including: levelling out of scree plot, eigenvalue threshold of  $> 1$ , parallel analysis, and factor loadings. If the number of axes to interpret is ambiguous, then the research team will use study specific knowledge to evaluate the results from the PCA to make decisions on which axes to include in further analysis. In step 2, we will analyze the composite scores

from the PCA analysis using the same GLMM approach as previously described with the exception that the distributional assumption will be normal with an identity link function. The estimate of interest will be the mean difference in PCA scores between the intervention and control. In addition to the PCA composite scores, we will also analyze the sum scores (i.e., the sum of the responses over all of the questions). The analytic approach will be the same for that as for the composite axes. If we find that our conclusions are similar between the two approaches (PCA and sum scores) then we will focus our interpretation on the sum scores as these provide more straightforward interpretation compared to the PCA composite scores, even though in theory PCA scores are more valid.

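### On a score capped at 12, the planned quantile regression cannot tell greater benefit for the worst-off clients from equal benefit for all, and it does not describe individuals

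*Combined protocol and SAP*

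**What the plan says.** The outcome is built from yes/no items. SAP section 4.0 states: "We will analyze 12 dichotomous (yes/no) patient experience questions from the trained exit client (TEC) survey". One planned summary is the sum score, "the sum of the responses over all of the questions", and the Figure S5 legend describes it as "the sum of responses to the 12 questions on the client experience survey (range 0 to 12"). The maximum is therefore 12.

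The quantile regression paragraph of SAP 4.0 proposes regression lines through chosen quantiles, naming the 90th and 10th percentiles as examples, "to test how individuals at distributional extremes respond to the intervention". It then adds: "We will also test whether the slope varies by the intervention by fitting a treatment x intervention interaction". It does not mention an upper bound, discreteness or a ceiling.

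Table S6 reports the fitted quantiles of the sum score for 632 control clients, 249 with up to 6 months of intervention and 230 with more than 6 months. The Figure S5 legend interprets them: "The greatest effects (i.e., change to mean sum score) were seen amongst clients who reported the worst experiences". It adds that little or no effect was seen above the 60th percentile. The Figure S1 legend says that client experience was measured cross-sectionally.

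**The concern.** The question asked is who benefits. A quantile difference on a bounded score also depends on how much room each quantile has left. If the control group already sits at or near 12 over the upper part of the distribution, the upper quantiles show little or no gain whatever the intervention does for those clients. A gradient that falls towards zero is then compatible with at least two accounts: clients with poor experiences gain more, or all gain alike and the ceiling hides it at the top.

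There is a second problem. Each quantile contrast compares the control and intervention score distributions. It describes how a person at an extreme responds only if clients would keep their rank under both conditions, which the plan neither states nor justifies.

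At stake is a statement about which clients gain most, which programmes may use when deciding where to direct effort.

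**Working it through.** **Inputs.** Control quantiles, differences for more than 6 months against control, and 95% intervals from Table S6. Item percentages from Table S5. Score maximum of 12 from the Figure S5 legend.

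**Step 1: reproduce the table.** Subtracting the control from the intervention value at each of the 19 quantiles returns the printed differences to within 0.1 (rounding), for both intervention periods.

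**Step 2: room to improve.** Room = 12 − control quantile. Examples: 12 − 5.9 = 6.1 at the 5th percentile; 12 − 11.2 = 0.8 at the 60th; 12 − 11.9 = 0.1 at the 75th and 80th; 12 − 12 = 0 from the 85th up. The 90th percentile, one of the SAP's two examples, cannot rise. Table S6 shows 0 (0 to 0) there.

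**Step 3: equal additive benefit, capped.** Suppose every client gains D points up to 12. The effect at a quantile is then min(D, room). I compared D from 0.1 to 3.9, in steps of 0.1, with the 19 pointwise intervals. For D = 1.1, 1.2 and 1.3 no interval is violated. The fit is tight: to the printed decimal, 1.1 is the lower limit at the 5th percentile, 1.3 is the upper limit at the median, and the 0.8 available at the 60th percentile equals its upper limit. D = 1.0 fails at the 5th percentile and D = 1.4 fails at the median.

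**Step 4: equal odds ratio on every item.** Model: 12 binary items with a normal client trait, calibrated to the control percentages of Table S5. The negative percentages sum to 211.0 in control and 92.5 after 6 months, so the raw mean scores are 12 − 2.110 = 9.89 and 12 − 0.925 = 11.08. One common logit shift is applied to every client and item so that the mean rises from 9.89 to 11.08. The trait SD is not in the documents; I assume 1.0 to 2.5. Quantiles are interpolated, because the raw score takes whole values only.

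| Quantile | Control | Room | Reported >6m (95% CI) | Capped shift 1.3 | Equal odds, SD 1.0 | Equal odds, SD 1.5 |
|---|---|---|---|---|---|---|
| 0.05 | 5.9 | 6.1 | 3.0 (1.1 to 4.9) | 1.3 | 2.5 | 3.2 |
| 0.10 | 7.3 | 4.7 | 2.2 (0.7 to 3.7) | 1.3 | 2.2 | 2.8 |
| 0.20 | 8.6 | 3.4 | 1.4 (0.3 to 2.5) | 1.3 | 1.8 | 2.1 |
| 0.30 | 9.3 | 2.7 | 1.3 (0.4 to 2.2) | 1.3 | 1.5 | 1.6 |
| 0.50 | 10.6 | 1.4 | 0.6 (−0.1 to 1.3) | 1.3 | 1.0 | 0.8 |
| 0.60 | 11.2 | 0.8 | 0.0 (−0.8 to 0.8) | 0.8 | 0.8 | 0.6 |
| 0.70 | 11.5 | 0.5 | 0.0 (−0.9 to 0.9) | 0.5 | 0.6 | 0.5 |
| 0.80 | 11.9 | 0.1 | 0.0 (−0.4 to 0.4) | 0.1 | 0.4 | 0.1 |
| 0.90 | 12 | 0 | 0 (0 to 0) | 0 | 0.0 | 0.0 |

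Control and Room are Table S6 values. The simulated control quantiles differ slightly (for example 11.2 at 0.70 with SD 1.0), which is why a simulated gain can exceed the listed room.

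With SD 1.5 all 19 effects lie within the reported intervals. With SD 1.0 only the 85th percentile falls outside (0.2 against an interval of zero width). With SD 2.0 and 2.5 the effects at some low quantiles exceed the reported upper limits, and the simulated control 5th percentile (3.7 and about 2.9) also falls well below the 5.9 in Table S6. Over the whole range of SDs the effect runs from 2.5 to 3.8 at the 5th percentile, through 0.5 to 1.0 at the median, to 0.0 at the 90th and 95th.

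**Step 5: what the ceiling does not explain.** Between the 5th and 30th percentiles the reported effect falls from 3.0 to 1.3, while at least 2.7 points of room remained. A capped additive shift is flat there. At the 60th to 70th percentiles 0.5 to 0.8 points of room remained and the estimate was still 0.0, where the capped shift gives 0.5 to 0.8. The intervals are too wide to settle either discrepancy.

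**The case against.** The strongest reply has five parts.

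- **Accurate on its scale.** Figure S5 defines effects as change in the sum score. A client with 12 of 12 positive answers has no negative answer left to remove. Under an equal odds ratio, low scorers really do gain more points. This stands: whether an effect is equal depends on the scale, and the shifts at low quantiles are valid descriptions of the distribution.
- **The ceiling is visible.** The legend gives the range and the table prints 12 for control. That helps a careful reader, but the legend's sentence still draws the inference about who benefits.
- **Lower-tail benefit is analysed separately.** Table S4 reports an adjusted risk difference of −16.9 percentage points (−24.8 to −8.9) for scores of 8 or less. That supports fewer bad experiences. It does not show that the benefit is greater there than elsewhere.
- **Hindsight.** The paragraph does not name the sum score, gives the percentiles only as examples, and component scores were also planned. Where the ceiling lies is known only from results. That 12 yes/no items have a maximum was known when the SAP was written.
- **Supplementary analysis of a secondary outcome.** This stands. The primary outcome and the mean difference in sum score are untouched.

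A reader might infer that the ceiling produces this gradient under any benefit, so that Table S6 says nothing about who gains. The documents do not support that. As step 5 shows, an additive ceiling causes neither the fall below the 30th percentile nor the 0.0 at the 60th. A reader might also infer that the interaction cannot be fitted, since a term multiplied by itself is redundant. The same paragraph fits a line over the course of the study and asks whether its slope differs by intervention, so time by intervention is evidently meant; it is a slip to correct.

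**Conclusion.** The concern holds in a limited form. On the 0 to 12 score the planned test cannot answer its stated question at the upper end: room is 0.8 points at the 60th percentile, 0.1 at the 75th and 80th, and none from the 85th up. The reported gradient cannot distinguish greater benefit for the worst-off from equal benefit under a ceiling, whether equal means 1.1 to 1.3 points or a common odds ratio. It does not rule out real heterogeneity. The inability to move is strict only upwards and from the 85th percentile.

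The cross-sectional design separately rules out reading the shifts as responses of individuals unless ranks are assumed to be preserved. Protocol section 7.0 allows one person to be surveyed before and after crossover, but the SAP model has a facility random effect and no client-level term, so it makes no within-person comparison.

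Assumptions: the Table S6 quantiles are taken as printed; the intervals are pointwise and are used as a check of compatibility, not as a joint test; the item model assumes a normal trait and ignores facility clustering and period, neither of which changes the maximum of 12.

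**What to change.** 1. Keep the quantile regression on the sum score, labelled descriptive. Print the maximum possible shift (12 minus the control value) beside each quantile in Table S6 and Figure S5.
2. Reword the SAP paragraph and the Figure S5 legend so that they describe shifts in the score distribution, not effects in clients or individuals at an extreme. Add that equal benefit under a ceiling could give a similar pattern.
3. Correct the interaction to time by intervention.
4. Add, without replacing the quantile results, one model that respects the bound. An example is an ordinal or beta-binomial mixed model for the number of negative answers out of 12, with a facility random effect and period. In the ordinal version, let the intervention effect vary by cut-point to examine heterogeneity. State the scale on which an effect counts as equal, because the answer depends on it.

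Cost: some rewording and one extra model on data already collected. The downside is that the statement about who gains most becomes weaker.
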